**SUPERVISORS:**

[name]

[name] [name]

[name]

Table of Contents

1.0 Introduction 3

2.0 Study Overview 4

2.1.1 Methodology 4

2.1.2 Components of the Treatment 5

2.1.3 Design 7

2.1.4 Patient Selection and Inclusion/Exclusion Criteria 7

2.1.5 Sample size determination 8

2.1.6 Statistical analysis 8

3.0 Justification of methodology 8

4.0 Feasibility 9

4.1.1 Study committe 9

4.1.2 Setting 9

4.1.3 Time Line 10

5.0 Ethics 10

6.0 Funding 10

Appendix A: Brief Cope 11

Appendix B: SDSCA 12

Appendix C: AADQ 13

References ….14

1. **INTRODUCTION**

According to the American Diabetes Association (2013) the economic costs of diabetes are high. The estimated total economic cost of diagnosed diabetes in 2012 is $245 billion, a 41% increase from our previous estimate of $174 billion (in 2007 dollars). Type 2 diabetes is a chronic disease associated with a ten-year-shorter life expectancy and the most common form of diabetes (Paris et al, 2001).This is partly due to a number of complications with which it is associated, including: two to four times the risk of [cardiovascular disease](https://en.wikipedia.org/wiki/Cardiovascular_disease), including [ischemic heart disease](https://en.wikipedia.org/wiki/Ischemic_heart_disease) and [stroke](https://en.wikipedia.org/wiki/Stroke); a 20-fold increase in lower limb [amputations](https://en.wikipedia.org/wiki/Amputations), and increased rates of [hospitalizations](https://en.wikipedia.org/wiki/Hospitalization) (Melmed et al, 2011). Diabetes control requires continuing medical care and patient self-management education to reduce the risk of long-term and acute complications (Jaser et al, 2012).

In addition to medical treatment, many kinds of psychological interventions have been used in the control of diabetes, including self-care education (Funnell & Anderson, 2004), behavior therapy (Tate, Jackvony & wing, 2003), and cognitive-behavior therapy (Snoke et al, 2001); these have been effective, but unfortunately mostly for short periods of time (Rubin & Napora, 2001); Furthermore, previous research studies have been conducted with no clear depiction of the real social and cultural situations and contexts making it difficult for those working in other healthcare settings to adapt the program to their own situations (Bastiaens et al, 2009).

Acceptance and commitment therapy in comparison to other interventions is more consistent with the chronic nature of the diabetes. it seems impossible to eliminate thoughts related to diabetes that are part of the very nature of the disease, However, most psychological studies involving the application of cognitive-behavior therapy have concentrated on decreasing, changing or stopping negative thoughts related to diabetes, but, Acceptance and commitment therapy focuses on the acceptance of thoughts that emphasize clarification of values and personal goals (Gregg et al, 2007).

Acceptance and commitment therapy were used successfully to lifestyle changes in behavioural problems (Hayes et al, 2004 ; Niemeier et al, 2012) but, to date only a limited number of studies has been published investigating the effects of Acceptance and commitment therapy on diabetes self-management (e.g. Gregg et al, 2007), emphasizing the need for related data. In spite of different studies on acceptance and commitment therapy, the role of moderator variables in the process of testing the effectiveness of ACT in diabetes control has not been addressed in the literature. Therefore, our purpose is assessment of one of the important moderators (coping style) in the effect of psychotherapy on self-management. Promising results support the continued use and development of the method.

***Purpose and benefits of the study***

This study has two purpose:1- To examine whether acceptance and commitment therapy works for participants with a diagnosis of type 2 diabetes and whether it provides clinically significant improvement in HbA1c reduction and improvement in self-management compared with the control group. 2- To assess the moderating role of coping styles in the relationship between acceptance and commitment therapy and self-management of patients with type 2 diabetes.

Perhaps the main contribution the study could give is that it opens up for other psychological modator and mediators in the effect of acceptance and commitment therapy on development of diabetes control. Therefore, this study may become important. this will be important information as many Mindfulness-Oriented Therapist already engaged in acceptance and commitment therapy

1. **PROPOSED STUDY**

This randomised controlled trial will evaluate the efficacy of acceptance and commitment therapy to effectively control diabetes. This will be an intervention trial using treatments and one-day educational workshop. The study sample will be randomised into two arms: treatment and control. The study population will consist of 100 patients with type 2 diabetes.

## Study Overview

### 2.1.1 Methodology

Setting and Participants: The setting for this study will be the Endocrine Department of Labbafinejad Hospital in Tehran. The study will involve patients with type 2 diabetes. The study population will be male and female, in the age groups from 40 to 60. Sampling and Recruitment: Recruitment for the study will be facilitated by Labbafinejad Hospital. Participants will be introduced to researchers by the endocrinologist from the endocrine department. Interested parties will be encouraged to contact the psychologist directly and provide their name, phone number and preferred time of contact. Interested participants will be given an Information Kit, which will include: a sample consent form, a Backgrounder explaining the purpose of the study and contact list and phone numbers of the psychologist and researchers involved in the study.

Interested participants will be encouraged to ask questions to their Endocrinologist and directly to the Psychologist. The participants will be introduced to researchers by the endocrinologist from the endocrine department to participate in a 1-day educational workshop for self-management of diabetes,and all participants will be received a one-day workshop about diabetes control and will be encouraged to complete several questionnaires on socio-demographic characteristics, Summary of Diabetes Self-Care Activities (SDACA), Beck Depression Inventory, Acceptance and Action Diabetes Questionnaire and Brief COPE Questionnaire. then weight and height will be measured and blood samples will be obtained. Eligible participants will be randomly assigned to either the control or treatment groups (using the random number table), and will be booked for further appointment times.

On subsequent visits, the intervention group patients will receive treatments including group acceptance and commitment therapy (ACT) for diabetes management in addition to the one day workshop. the ACT will be delivered during 10, 2-hour sessions. the control group patients will receive one day workshop to help diabetes control and they will be remained in a waiting list and will be received same treatment after the end of study (because of clinical ethical concern, but these result will not be entered into analysis). In one day workshop, both groups will be encouraged to engage in an active exercise routine. Both groups continue will be medications (e.g., Metformin), but they can be not changed medications and dosages during the study. Information of both groups will be obtained by questionnaires and results from blood tests at the points, before beginning therapy, after completing therapy sessions, and last, at a three-month follow-up. Blood test assessments will be provided for free as an incentive for participation.

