| 4 | Share information about value of diabetes control in Group  Exercise: Talking with your tombstone | Cognition of key values and goals in diabetes control and specific actions related to those goals |
| 5 | A discussion about values  Tichener's Milk, Milk, Milk Exercise | Improving control of diabetes on the basis of values or the ability to distinguish the literal meaning of words and values |
| 6 | A discussion about experiential avoidance  Exercise: The Polygraph Metaphor | Recognizing negative thoughts and process of experiential avoidance |
| 7 | Share the experience of cognitive avoidance  Exercise: Chinese Handcuff Metaphor | Improving recognizing experiential avoidance and appropriate coping |
| 8 | A discussion about acceptance of negative thoughts related to disease  Exercise: Chessboard Metaphor | Internalization of acceptance process during self-care activities and adjusting to diabetes |
| 9 | A discussion about the ingredients of acceptance  Activity: goal identification | Improving acceptance of diabetes-related negative feeling and thoughts |
| 10 | A discussion about commitment to managing diabetes  Activity: Stand and commitment to change behavior | Make a commitment to managing your diabetes |

Follow-up data will be collected at 3 month post treatment via questionnaire package containing Summary of Diabetes Self-Care Activities (SDACA), Acceptance and Action Diabetes Questionnaire and Brief COPE Questionnaire. Generally, endocrinlogist appointments is every 3 months, therefore appointments will be synchronized with time of post test and follow up that it will be faciliteted the collection of data.

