**Inclusion criteria**

1) Age 40-60 at study entry

2) Men and women

3) Written and informed consent.

4) Patients must have an Endocrinologist that they have seen in every 3 months.

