**Exclusion criteria**

1) Have other kinds of diabetes (type 1 and Gestational diabetes)

2) If they had been hospitalized

3) Lack of satisfaction could not collaborate or continue in the study.

4) Any current serious disorders determined to be clinically significant to the study.

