**2.1.5 Sample size determination**

According to a meta-analysis study in diabetes interventions; Brown (1990), the required sample size, based on a power of 80% and a 2-tailed α of 0.05, was calculated 35 individuals per group. However, assuming a 10% loss to follow-up rate, we need 45 subjects per group to commence the trial.

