# Justification of Methodology

The study trial shall involve 100 patients with type 2 diabetes as determined above. The trial shall last 22 weeks (10 weeks treatment time and 12 weeks follow-up) which we realized enough time to determine whether a clinically significant effect will be produced. We employed a randomized controlled design to determine if any change is significantly different from a control group not receiving the acceptance and commitment therapy. Control group allow us to determine if variability in diabetes control within individuals has overshadowed the impact of potential confounders. Examples of factors that could influence variability within individuals include age, sex, educational level, diabetes duration and medical treatment.

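### The medication freeze in Section 2.1.1 has no safety exception and does not say whether it binds the endocrinologist as well as the patient

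*Protocol*

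**What the plan says.** Section 2.1.1 of the Protocol states the rule for both arms: they stay on their existing drugs (metformin is the example), "but they can be not changed medications and dosages during the study". The same section plans questionnaires and "results from blood tests at the points, before beginning therapy, after completing therapy sessions, and last, at a three-month follow-up".

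The inclusion criteria require ongoing specialist care: "Patients must have an Endocrinologist that they have seen in every 3 months". Section 2.1.2 says these "appointments will be synchronized with time of post test and follow up". The Justification of Methodology gives the schedule: "The trial shall last 22 weeks (10 weeks treatment time and 12 weeks follow-up". HbA1c is a stated outcome in the purpose of the study and in Section 2.1.6.

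The exclusion criteria cover hospitalisation, patients who "could not collaborate or continue in the study", and current serious disorders. None of them mentions a change of medication.

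**The concern.** A rule that fixes drugs and doses is a treatment restriction, so any safety exception belongs next to it in the protocol. A statistical analysis plan could say how medication changes are analysed. It could not authorise a clinician to make one.

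The trial's own procedures can reveal the need for a change. Blood is taken after the therapy sessions, and an endocrinologist appointment is timed with that visit. The entry criteria set no numerical HbA1c limit. Both arms are encouraged to exercise, and the ACT arm also works on diet and physical activity, so glucose may move while the dose is held fixed. A need to lower a dose is as foreseeable as a need to raise one.

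What is at stake is first the safety of such a patient, in either arm. Second is consistency: with no stated rule, similar patients may be handled differently, and nothing provides for a record of what was done.

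**Working it through.** The Protocol gives no figure of its own on this point. The check is mainly a comparison of sections, with short arithmetic on time and numbers.

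**1. Is there an exception?** Sections 2.1.1 and 2.1.2, the entry criteria and the Justification of Methodology were read together. They contain no rescue rule, no dose-adjustment rule and no statement that the endocrinologist may override the freeze. The exclusion criteria offer ways out of the study but do not lift the rule for a patient who stays in.

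**2. Whom does the rule bind?** The grammatical subject is the two groups of patients. Read that way, it may only forbid patients to adjust their own doses. Read as a condition on treatment during the study, it also stops the endocrinologist. The text does not decide between the two.

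**3. When could a need come to light, and how long would it wait?** This step assumes that the rule binds the endocrinologist and runs to the follow-up visit.
- *Before therapy.* Section 2.1.1 describes blood sampling first and random assignment of eligible participants afterwards. That order allows a need seen at baseline to be met before entry.
- *At post-test.* Post-test is at week 10 and follow-up at week 10 + 12 = 22. Wait = 22 − 10 = **12 weeks**.
- *Between post-test and follow-up.* The wait is shorter than 12 weeks.
- *During the treatment weeks.* A need showing itself at week t would wait 22 − t weeks. No scheduled blood test falls there, so it would have to surface through symptoms or outside care, and no figure is put on it.

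The Time Line section gives twelve weeks of direct involvement and six months for the trial, which does not match 22 weeks. The 12-week figure is the interval from post-test to follow-up, which Sections 2.1.1 and 2.1.2 also put at three months. The point does not depend on resolving that mismatch.

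**4. What can the patient do?** Under the stricter reading there are three routes: go without the change, deviate, or leave. The exclusion criterion on not being able to continue hints at leaving, but no section says which is intended.

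**5. Would exits endanger the planned size?** Section 2.1.5 needs 35 per group and says: "assuming a 10% loss to follow-up rate, we need 45 subjects per group to commence the trial".
- At 45 per group: 45 − 35 = 10 in reserve; 10% loss uses 0.10 × 45 = 4.5; 10 − 4.5 = 5.5, so 5 further exits per arm are absorbed.
- With the 100 patients stated elsewhere ("The study population will consist of 100 patients with type 2 diabetes"), 50 per arm: 50 − 35 = 15; 10% loss uses 5; 15 − 5 = 10 further exits per arm are absorbed.

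Nothing in the Protocol suggests exits on that scale.

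**The case against.** The best answer is that the sentence speaks of patients, not doctors. The patients come from an endocrinology department, must be under three-monthly specialist care, and keep their appointments during the trial. On that view ordinary care goes on and only self-adjustment is barred. This stands as a possible reading, and it limits the point to a conditional one. It does not remove the point, because no section says that doses may be adjusted at those appointments. A safety-relevant rule should not depend on which reading a clinician happens to choose.

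A second answer is that stable background medication is a recognisable way to isolate the effect of ACT on HbA1c. That also stands, and is why stability should remain the default.

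Third, one part of the Protocol (by the contents list, probably the study committee section), the consent pages and the information kit are not visible. Absence is therefore established only for the visible text.

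A reader might also infer three stronger things that the documents do not support:
- *A patient could wait the full 22 weeks.* For a need seen at baseline, the order of blood sampling and randomisation allows action before entry. A wait of that length would also require nothing to be done at the week-10 appointment.
- *The freeze biases the HbA1c comparison.* If the rule is followed, medication does not differ between arms among those who stay. If it is not followed, the documents give neither size nor direction.
- *The freeze threatens the sample size.* The reserve above absorbs 5 to 10 further exits per arm.

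**Conclusion.** The point holds as a defect in a stated rule: drugs and doses are frozen in both arms, no safety exception is visible, and the text does not say whether the endocrinologist is bound. If the endocrinologist is bound, a patient with clinically important high or low glucose at the post-test visit faces a wait of up to about 12 weeks, a deviation, or exit. If only patients are bound, the remaining fault is unclear wording, which the same sentence repairs.

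The 12 weeks rest on the schedule in the Justification of Methodology and on the freeze lasting until follow-up. How many patients would need a change cannot be derived from the documents. For a patient who needs none, the rule does no harm. No bias of any stated size or direction and no loss of planned size is claimed. The point merits correction because it concerns safety and the correction is cheap.

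**What to change.** Replace the sentence in Section 2.1.1 with: *Patients keep glucose-lowering medication and dosage stable during the study and do not change them on their own; the endocrinologist may change them when clinically necessary for safety.*

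Record each change (drug, direction, date, reason) at post-test and follow-up in both arms. Keep these patients in follow-up and in the group to which they were randomised.

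A fixed HbA1c limit as a trigger is best left out. HbA1c is an outcome, so such a trigger would make treatment changes depend on the outcome and could dilute the follow-up contrast. Clinical judgement is enough for safety.

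The practical cost is one sentence and one record line at two visits already aligned with endocrinologist appointments, with no added patients or visits. The scientific cost is that medication is no longer constant by design. If more controls than ACT patients are escalated, the follow-up HbA1c difference may shrink. It should then be read as the effect of assignment to ACT with needed medication changes allowed, and the record helps interpret such a shift without removing it. That HbA1c is measured at follow-up is inferred from the blood tests in Section 2.1.1 and the outcomes in Section 2.1.6, since Section 2.1.2 lists only questionnaires at that visit.

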**2.1.2 Components of the Treatment**

The group acceptance and commitment therapy (ACT) will be delivered during 10, 2-hour sessions and each session of study is one week.

Across problems in living, ACT is a treatment that is difficult to deliver with integrity. The application of ACT to diabetes is no different, and contains specific challenges as well. The goal of the treatment is to compassionately assist patients in dealing with any thoughts, feelings, worries, anxieties, or fears they may have related to their disease and its maintenance in order to help them live their life in a valued direction related to their diabetes. A key first step in this holistic approach to diabetes self-management is to provide adequate information about how to care for one’s diabetes in order to address the specific motivational and acceptance pieces laid out in the treatment. Thus, the first half of the treatment provides specific information regarding the management of diabetes and the second half of the treatment addresses motivational and acceptance issues related to engaging in self-management behaviors. The treatment is divided into 5 main modules:

Module I: Education and Information

Module II: Food, Diabetes, and Your Health

Module III: Exercise and Diabetes

Module IV: Coping and Stress Management

Module V: Acceptance and Action

Each module can be compared to two treatment session and will be administered at weekly intervals. In the first three modules, patients are given broad information about diabetes and its complications, and are given specific information about the effects of high and low glucose on one’s body. In the second module, this information is tied specifically to the intake of food and information is provided about how to eat in order to prevent surges and dips in blood glucose. In the third module, information is provided about the impact of exercise on blood glucose, and setting up an exercise routine. Once the broad and specific information on diabetes is given, the second half of the treatment addresses more psychological and motivational barriers to effective self-management. The fourth module addresses avoidance coping as it relates to diabetes, and particularly addresses avoidance of negativelyevaluated thoughts and feelings in diabetes, and how they may interfere with effective self-management. The fifth module integrates the didactic and acceptance elements of the treatment and focuses patients on moving in the direction of their values. In addition to being specifically addressed in the fifth module, values are targeted throughout the treatment and are a major component of the intervention. Specifically, directing patients toward values-directed behavior change in diabetes self-management is the overall task of the treatment, with diabetes-related information and information about accepting negatively-evaluated thoughts and feelings (Gregg, 2004; available at http://www.psych.sjsu.edu/_jgregg).

Overall structure for each session:

| Session | Activity & Exercises | Purposes |
| --- | --- | --- |
| 1 | A general introduction of all the members of the group  Activity: self-assessment of diabetes care | Member recognition to facilitate of therapeutic relationship  Identification of information level of group about diabetes control |
| 2 | Share nutritional information in Group  Exercise: Values and choices in nutrition | Internalization of nutritional information and its effect on blood sugar |
| 3 | Share physical activity information in Group  Exercise: A choice of physical activity | Internalization of physical activity Information and its effect on blood sugar |
| 4 | Share information about value of diabetes control in Group  Exercise: Talking with your tombstone | Cognition of key values and goals in diabetes control and specific actions related to those goals |
| 5 | A discussion about values  Tichener's Milk, Milk, Milk Exercise | Improving control of diabetes on the basis of values or the ability to distinguish the literal meaning of words and values |
| 6 | A discussion about experiential avoidance  Exercise: The Polygraph Metaphor | Recognizing negative thoughts and process of experiential avoidance |
| 7 | Share the experience of cognitive avoidance  Exercise: Chinese Handcuff Metaphor | Improving recognizing experiential avoidance and appropriate coping |
| 8 | A discussion about acceptance of negative thoughts related to disease  Exercise: Chessboard Metaphor | Internalization of acceptance process during self-care activities and adjusting to diabetes |
| 9 | A discussion about the ingredients of acceptance  Activity: goal identification | Improving acceptance of diabetes-related negative feeling and thoughts |
| 10 | A discussion about commitment to managing diabetes  Activity: Stand and commitment to change behavior | Make a commitment to managing your diabetes |

Follow-up data will be collected at 3 month post treatment via questionnaire package containing Summary of Diabetes Self-Care Activities (SDACA), Acceptance and Action Diabetes Questionnaire and Brief COPE Questionnaire. Generally, endocrinlogist appointments is every 3 months, therefore appointments will be synchronized with time of post test and follow up that it will be faciliteted the collection of data.

